## Abstract

**Background:**

Rates of surgical site infections (SSIs) following groin incision for femoral artery exposure are much higher than expected of a clean operation. The morbidity and mortality is high, particularly with the use of prosthetic grafts. The vascular surgery population is at an increased risk of SSIs related to peripheral vascular disease (PVD), diabetes, obesity, previous surgery and presence of tissue loss. Negative pressure wound therapy (NPWT) dressings have been used on primarily closed incisions to reduce surgical site infections in other surgical disciplines. We have not come across any randomized controlled trials to support the prophylactic use of negative pressure wound therapy in high-risk vascular patients undergoing lower limb revascularization.

**Methods/design:**

In this single-center, prospective randomized controlled trial, patients scheduled for a lower limb revascularization requiring open femoral artery exposure who are at a high risk (BMI > 30 kg/m^2^, previous femoral cutdown or Rutherford V or VI category for chronic limb ischemia) will be eligible for the study. A total of 108 groin incisions will be randomized to the use of a negative pressure wound device or standard adhesive gauze dressing. Patients will be followed in hospital and reassessed within the first 30 days postoperatively. The primary outcome is SSI within the first 30 days of surgery and will be determined using the intention-to-treat principle. Secondary outcomes include length of stay, emergency room visits, reoperation, amputation and mortality. A cost analysis will be performed.

**Discussion:**

The trial is expected to define the role of NPWT in SSI prophylaxis for lower limb revascularization in high-risk vascular patients. The results of the study will be used to inform current best practice for perioperative care and the minimization of SSIs.

**Trial registration:**

NCT02084017, March 2014

## Background

Surgical site infections (SSIs) at the groin incision following lower extremity revascularization procedures have been reported as up to 30 % [1–6]. This is significantly higher than expected in a surgical wound classified as clean, 2.1–3.3 % [7]. A number of risk factors within this population has been identified as risk factors for SSIs and include obesity, previous femoral cutdown and presence of critical limb ischemia [8, 9]. Significant morbidity associated with SSIs in lower extremity revascularization includes increased length of stay, sepsis, hospital readmissions, limb loss, and death [10, 11]. Further, the cost of vascular SSIs has been recently estimated to add US$10,000 to the cost of care per patient [11].

A variety of methods including topical antibiotics, antibiotic-impregnated grafts, and platelet-rich plasma have all been used with limited success [12]. Negative pressure wound therapy (NPWT) is a relatively new treatment modality that has also demonstrated some evidence in SSI prevention in incisions closed primarily, including groin incisions [6, 13, 14]. However, there are currently no randomized controlled trials investigating the use of NPWT to prevent SSIs following lower limb revascularization.

The objective of this study is to assess the role of NPWT, using the Prevena Incision Management System (Kinetic Concepts Inc, San Antonio, TX, USA), in primary closed groin incisions in patients requiring femoral artery exposure for lower limb revascularization on decreasing SSI compared to standard sterile gauze dressing. We hypothesize that patients randomized to NPWT will have a lower incidence of SSI in the groin incision within the first 30 days of surgery compared to patients randomized to the control group.

### Study design

This will be a single institution, prospective, randomized, open-label trial, in which eligible patients will be randomized to NPWT or a standard dressing of groin incision using a block randomization.

### Study setting

The study will take place at the Victoria Hospital of London Health Sciences Center (LHSC) in London, ON, Canada: Victoria Hospital is an academic teaching hospital and is associated with the Schulich School of Medicine and Dentistry at Western University.

### Eligibility

High-risk patients scheduled for a lower limb revascularization requiring groin incision for a femoral artery exposure are eligible for the study. Example operations include but are not limited to femoral to femoral artery crossover bypass, femoral to distal artery bypass, and femoral artery endarterectomy. Before the enrolment, informed consent will be obtained from each patient. Primary author KL will identify and be responsible for enrolling all the eligible patients.

### Inclusion criteria

Patients must be 18 years or older and scheduled for a lower limb revascularization operation requiring femoral artery exposure. Groin incision must be closed primarily in the operating room. Patients with one of the high-risk factors: obesity (body mass index > 30 kg/m^2^), previous femoral artery exposure or presence of minor or major tissue loss, will be included in the study.

### Exclusion criteria

Patients who have a pre-existing groin infection, a known sensitivity/allergy to adhesive material or on whom a complete seal of NPWT cannot be obtained at the time of device application will be excluded.

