### Intervention and control

The intervention group will have NPWT, the Prevena Incision Management System (Kinetic Concepts Inc, San Antonio, TX, USA), applied to the primary closed groin incision. The Prevena system has a silver interface with a foam layer connected to a small portable battery-operated vacuum unit. The vacuum is preset to continuous at 125 mmHg. The device is applied under sterile conditions in the operating room and remains on the patient until the hospital discharge or postoperative day 8, whichever occurs first. The wound will be inspected for any evidence of infection once the Prevena is removed. The device is used only once and is disposed of at the end of the study. Any concern about the wound or the device will require removal of the NPWT earlier than planned and will be recorded as a secondary endpoint of the trial.

The control group will have a standard sterile gauge dressing to cover the groin incision. The postoperative management is typically removal of the dressing on day 2 postoperatively with daily dressing changes thereafter. All other pre- and postoperative care of patients will be the same in both groups. Hair will be removed with electric clippers preoperatively. Skin preparation will be done with 2 % chlorhexidiene. Every patient will received preoperative antibiotics (cephalexin or vancomycin if penicillin allergy is present) and postoperative antibiotics will be given for 48 h. At the end of the operation, the groin incision will be primary closed with either skin staples, monocryl or prolene sutures.

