### Randomization, allocation concealment and blinding

Once the groin incision is primary closed, randomization will be done using internet-based software, sealedenvelope.com (London, UK), via random permutated blocks. If the patient has bilateral groin incisions, the right groin will be randomized and the left groin will be automatically placed in the other arm. The surgical team, clinical staff, and patient will not be blinded to the intervention status. The primary outcome of SSI will be assessed by a clinical specialist nurse who will be blinded to the intervention status.

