### Statistical analysis

All analysis will be prespecified and conducted according to the intention-to-treat principle with the use of SPSS version 20 (IBM, Armonk, NY, USA). Each incision will be randomized to the NPWT or standard dressing group. In the case that a patient requires bilateral incisions, the right side will be randomized and the left side will be automatically placed in the opposite arm but not be included in the primary analysis as there is a loss of independence. Baseline characteristics of the two groups will be recorded. The continuous variables will be compared using Student’s *t* test. The categorical variables will be compared using Pearson’s chi-square or Fisher’s exact test depending on the number of events. The proportion of SSIs amongst randomized groins will be compared between the NPWT and standard dressing groups using a chi-square test or Fisher’s exact tests depending on the number of events. An absolute risk increase/reduction for SSI will be presented for the use of NPWT, as well as the number needed to treat to prevent a single SSI. Patients lost to follow-up have the outcome last assessed treated as his or her final outcome. A secondary analysis will be performed including the nonrandomized groin in patients with bilateral incisions. We will also perform a subgroup analysis on just patients undergoing bilateral incision using McNemar’s test.

Secondary outcomes will be compared between groups using a chi-square test for categorical variables. Non-normally distributed continuous variables will be compared using the Mann–Whitney *U* test. A *p* value of less than 0.05 will be considered significant and all tests will be two-sided.

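### Failure to obtain an NPWT seal is an exclusion that can arise only after randomization and only where the device is applied, which conflicts with the stated intention-to-treat analysis

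*Protocol article*

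**What the plan says.** Four parts of the protocol article bear on this.

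- **Exclusion criteria:** patients "on whom a complete seal of NPWT cannot be obtained at the time of device application will be excluded".
- **Randomization, allocation concealment and blinding:** "Once the groin incision is primary closed, randomization will be done using internet-based software". In a bilateral patient the right groin is randomized and the left takes the other arm. The same section adds: "The surgical team, clinical staff, and patient will not be blinded to the intervention status".
- **Intervention and control:** "The intervention group will have NPWT", and "The device is applied under sterile conditions in the operating room". For the comparator, "The control group will have a standard sterile gauge dressing to cover the groin incision". No seal test is described for controls, and none before allocation.
- **Statistical analysis:** "All analysis will be prespecified and conducted according to the intention-to-treat principle". The abstract says of the primary outcome that it "will be determined using the intention-to-treat principle".

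Two related statements: early removal of the device is recorded as a secondary endpoint (Intervention and control), and the sample size is raised partly to allow for device malfunction (Sample size). Neither says what happens in the analysis to a groin that never sealed.

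**The concern.** An exclusion criterion is harmless to the comparison when it is settled before allocation, or when it is applied identically and blindly to both arms. This one is neither. A unilateral control groin has no device and so can never meet it. If the criterion is applied as written, the NPWT arm loses the groins on which the device could not be made to work, while their counterparts in the control arm stay in. The arms being compared are then no longer those that randomization created.

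The decision also lies with people who know the allocation. The Discussion explains that randomizing after closure is meant to limit bias from the surgical team; an exclusion judged by that team after allocation reopens the same route. Device failure is also handled inconsistently: a device taken off early is counted as an outcome, whereas one that fails at application removes the patient.

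At stake are the primary comparison, the risk reduction and the number needed to treat.

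**Working it through.** **1. Order of events.** Closure, then randomization, then device application (NPWT groins only), then the seal result, then exclusion. The trigger is therefore post-randomization and specific to NPWT application.

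**2. The plan's own figure.** Inputs from Sample size and Statistical analysis: 30% versus 6%, two-sided alpha 0.05, 80% power, Fleiss method with continuity correction.

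- Uncorrected: n = [1.96·√(2·0.18·0.82) + 0.842·√(0.30·0.70 + 0.06·0.94)]² / 0.24² = 39.03.
- Corrected: (39.03/4)·[1 + √(1 + 4/(39.03·0.24))]² = 46.99, so 47 per group against 48 stated.
- Inflation: 48/0.9 = 53.3, so 54 as stated.

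The sample-size arithmetic is not in question.

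**3. If NPWT works as planned.** Let f be the share of NPWT groins that do not seal and u their infection rate. The documents give neither, so both are assumptions. Take 30% in controls and 6% in sealed NPWT groins (applying the planning rate to sealed groins is also an assumption).

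- Intention-to-treat NPWT rate = (1 − f)·6% + f·u
- Overstatement caused by the exclusion = f·(u − 6%)

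Power is for 54 per arm, without continuity correction.

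| f | u | NPWT rate, all groins kept | Risk difference | Overstatement (points) | Power |
|---|---|---|---|---|---|
| 5% | 22% | 6.8% | 23.2 | 0.8 | 88.6% |
| 5% | 30% | 7.2% | 22.8 | 1.2 | 87.2% |
| 10% | 22% | 7.6% | 22.4 | 1.6 | 85.6% |
| 10% | 30% | 8.4% | 21.6 | 2.4 | 82.3% |
| 15% | 30% | 9.6% | 20.4 | 3.6 | 76.6% |
| 20% | 22% | 9.2% | 20.8 | 3.2 | 78.5% |
| 20% | 30% | 10.8% | 19.2 | 4.8 | 70.2% |

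The analysis with the exclusion would show 24 points in every row (number needed to treat 4.2, against 4.4 to 5.2 in the rows with u = 30%). The planned design has 91% power on the same basis. The sign changes only when u is below 6%: at u = 3% the exclusion understates the benefit by 0.2 to 0.6 points for f of 5–20%.

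**4. If NPWT has no effect.** Take 30% in both arms and let unsealed groins carry k times the risk of sealed ones. The rate in retained NPWT groins is 30%/(1 − f + f·k).

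- k = 2: 30/1.05 = 28.6% at f = 5% and 30/1.20 = 25.0% at f = 20%, a spurious benefit of 1.4 to 5.0 points. The chance of a significant result favouring NPWT (two-sided chi-square test, exact enumeration, 54 controls against 51 or 43 retained NPWT groins) rises from about 2.5% to 3.7% and 7.8%.
- k = 1: no bias.
- k = 0.5: 30/0.975 = 30.8% and 30/0.90 = 33.3%, a bias of 0.8 to 3.3 points against NPWT.

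**5. Bilateral patients.** The criterion excludes patients, and every bilateral patient has one NPWT groin. If the right groin is randomized to control and the device on the left does not seal, the right control groin, which belongs to the primary analysis, is lost too. Steps 3 and 4 therefore describe unilateral patients.

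**The case against.** The strongest defence is that the criterion does not say the groin leaves the analysis. The article commits to intention-to-treat twice and enlarges the sample for device malfunction, so the authors may have meant only that such patients stop the device. That reading is possible, and for this reason the documents show an unresolved conflict rather than proof that groins are dropped. But no section says that unsealed groins stay in their arm, and extra incisions do not repair selective removal.

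A reader might infer that losses can fall only on the NPWT arm. That is exact for unilateral patients; in bilateral patients a control groin can go as well. What is one-sided throughout is the trigger.

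A reader might also infer that the exclusion must favour NPWT even if the device does nothing. The documents do not support that. They link obesity and previous femoral exposure to infection, not to seal failure, and every participant already carries at least one high-risk factor, so unsealed groins need not be much worse than the rest. With no true effect, the bias is zero at average risk and reverses below it. It remains plausible that features which raise infection risk also hinder sealing, and on the planning rates the direction holds unless unsealed groins have under 6% infection.

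Finally, the upper figures combine high seal failure with high risk and should be read against a planned effect of 24 points.

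**Conclusion.** The point stands as a design conflict in the primary analysis. The exclusion occurs after randomization, is triggered solely by NPWT application and is judged unblinded, so it cannot be reconciled with the stated intention-to-treat principle if it is applied as written. This holds whatever the direction of the bias.

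The likely direction favours NPWT. The overstatement is 0.8 to 4.8 points under assumed seal failure of 5–20% and infection of 22–30% in unsealed groins, with the protocol's 30% and 6% elsewhere. Under no true effect the sign depends on the prognosis of those groins. Because neither quantity is given, the actual size is unknown. The documents do not support a claim that a specific bias has occurred or that its direction is certain.

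**What to change.** Reconcile Exclusion criteria, Randomization and Statistical analysis as follows:

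- Remove seal failure as a ground for exclusion from the primary analysis, and state that every randomized groin is analysed in its allocated arm.
- Report failure to seal as a device outcome, alongside early removal.
- Limit any analysis without unsealed groins to a labelled per-protocol or sensitivity analysis.
- Recover 30-day outcomes for any groin already dropped, including control groins of bilateral patients. The Trial status section reports 46 patients enrolled, so this needs checking now.

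The amendment to the text is short. The statistical cost is a diluted effect, in proportion to seal failure. With 30% infection in unsealed groins, power at 54 per arm falls from about 91% to 87% at 5% failure and 82% at 10%. It falls further if failures are more frequent or at higher risk: about 72% at 10% failure with 50% infection, and about 51% at 15% with 60%. The observed seal-failure rate should therefore be reviewed, without reference to outcome by arm, to see whether 54 per arm is still enough.

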### Intervention and control

The intervention group will have NPWT, the Prevena Incision Management System (Kinetic Concepts Inc, San Antonio, TX, USA), applied to the primary closed groin incision. The Prevena system has a silver interface with a foam layer connected to a small portable battery-operated vacuum unit. The vacuum is preset to continuous at 125 mmHg. The device is applied under sterile conditions in the operating room and remains on the patient until the hospital discharge or postoperative day 8, whichever occurs first. The wound will be inspected for any evidence of infection once the Prevena is removed. The device is used only once and is disposed of at the end of the study. Any concern about the wound or the device will require removal of the NPWT earlier than planned and will be recorded as a secondary endpoint of the trial.

The control group will have a standard sterile gauge dressing to cover the groin incision. The postoperative management is typically removal of the dressing on day 2 postoperatively with daily dressing changes thereafter. All other pre- and postoperative care of patients will be the same in both groups. Hair will be removed with electric clippers preoperatively. Skin preparation will be done with 2 % chlorhexidiene. Every patient will received preoperative antibiotics (cephalexin or vancomycin if penicillin allergy is present) and postoperative antibiotics will be given for 48 h. At the end of the operation, the groin incision will be primary closed with either skin staples, monocryl or prolene sutures.

### Randomization, allocation concealment and blinding

Once the groin incision is primary closed, randomization will be done using internet-based software, sealedenvelope.com (London, UK), via random permutated blocks. If the patient has bilateral groin incisions, the right groin will be randomized and the left groin will be automatically placed in the other arm. The surgical team, clinical staff, and patient will not be blinded to the intervention status. The primary outcome of SSI will be assessed by a clinical specialist nurse who will be blinded to the intervention status.

### Definition of primary endpoint and outcome measures

The primary endpoint is the incidence of superficial SSI within 30 days of surgery. SSI is defined by the Center for Disease Control and Prevention (CDC) criteria [15] as: infection occurring within the first 30 postoperative days involving skin and subcutaneous tissue of the incision and at least one of the following:Purulent drainage from the incisionOrganisms isolated from an aseptically obtained culture of fluid or tissue from the incisionAt least one of the following signs/symptoms of infectionPain or tendernessLocalized swellingRednessHeatOR incision is deliberately opened by a surgeon (unless incision is culture negative)4.Diagnosis of SSI by the surgeon or attending physician

Once the SSI is identified, the Szilagyi classification of vascular wound infections will be used to classify to infection [16]. This classification categorizes vascular SSI based on dermal involvement (I), subcutaneous involvement (II) or arterial graft involvement (III).

SSI will be assessed daily, at discharge, and reassessed at the outpatient clinic within 30 days following the operation.

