### Secondary endpoints

Secondary endpoints include length of stay, emergency room visits, SSI requiring surgical intervention, deep SSI occurring within 90 days of an operation, limb amputation, and mortality. A cost analysis will also be performed using the average cost provided by LHSC for inpatients, return visits, and any surgical intervention. Outcomes related to potential harm will also be identified including local reaction to the NPWT device, and the need for early removal of the dressing.

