## Discussion

This trial is the first randomized controlled trial to investigate the role of NPWT in reducing the incidence of SSIs following surgery for lower limb revascularization in high-risk patients. Matatov et al. retrospectively reviewed 115 groin incisions in 90 patients who received either NPWT or adhesive gauze dressing following vascular procedure [6]. The authors demonstrated a reduction of SSI from 30 % to 6 % and no grade II or III infections in the NPWT cohort [6]. Our hypothesis is that high-risk patients in this study will see a similar benefit of reduction of SSIs.

Draining fluid following lower limb revascularization is not a new concept and in the past surgical drains placed deep in the wound have been investigated with randomized trials and meta-analyses, which did not show a reduced rate of SSI [17–19]. Significant research has been invested into the mechanism of action of NPWT on wound healing leading to four primary effects: macrodeformation; stabilization of the wound environment; reduced edema and microdeformation [17]. In conjunction with reticulated open-cell foam, such as used in the current study, NPWT can have a stimulatory effect on cellular proliferation and angiogenesis. Further, by actively removing excessive interstitial fluid and edema, it is thought secondary necrosis is reduced [18]. On a molecular level, cytokine and growth factor expression are modulated to an anti-inflammatory profile and culminate in angiogenesis, remodeling and granulation tissue [19]. The closed suction environment placed under sterile conditions also effectively separates the incision from the surrounding environment theoretically preventing the inoculation of environmental bacteria.

This trial will clarify the role of NPWT and its potential for reduction in SSI in groin incisions for lower limb revascularization. The major limitation of this trial is the inability to blind the surgical team and the patient. We will randomize the incisions once the incision is primary closed to reduce the bias that could occur from the surgical team.

The results of this trial will be used to determine the role of NPWT in the prevention of SSI. If this intervention is shown to be effective for the prevention of SSI in this high-risk population, significant benefit with respect to both patient morbidity and resource utilization may be achieved.

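### The primary endpoint is named superficial SSI in its defining section but is SSI of any depth elsewhere, so the text does not settle whether a deep or graft infection within 30 days is a primary event

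*Protocol article*

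**What the plan says.** All references are to the protocol article.

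- **Definition of primary endpoint and outcome measures** states: "The primary endpoint is the incidence of superficial SSI within 30 days of surgery". It then defines SSI by CDC criteria as "infection occurring within the first 30 postoperative days involving skin and subcutaneous tissue of the incision", plus at least one of several listed signs or a physician's diagnosis. An identified SSI is then given a Szilagyi grade, "based on dermal involvement (I), subcutaneous involvement (II) or arterial graft involvement (III".
- **Secondary endpoints** lists separately "deep SSI occurring within 90 days of an operation".
- **Abstract, Methods/design** says: "The primary outcome is SSI within the first 30 days of surgery".
- **Background** gives the hypothesis that patients on negative pressure wound therapy (NPWT) "will have a lower incidence of SSI in the groin incision within the first 30 days of surgery".
- **Randomization, allocation concealment and blinding** calls the outcome assessed by the blinded nurse simply SSI.
- **Sample size** uses groin SSI rates of 30% and 6% from an earlier cohort, without a depth limit.
- **Statistical analysis** says: "The proportion of SSIs amongst randomized groins will be compared between the NPWT and standard dressing groups".
- **Discussion** says that the authors of that cohort "demonstrated a reduction of SSI from 30 % to 6 % and no grade II or III infections in the NPWT cohort".

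**The concern.** The defining section and the list of secondary endpoints together divide infections by depth: superficial at 30 days is primary, deep at 90 days is secondary. Every other place that mentions the primary outcome makes no such division. The defining section also conflicts with itself, because a scale whose top grade is arterial graft involvement does not suit an endpoint limited to superficial infection.

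The difference decides which groins count as events. The Background justifies the trial by sepsis, limb loss and death after SSI, and the abstract stresses prosthetic grafts. Under a literal superficial-only rule, the infections behind that rationale could drop out of the primary comparison. Two analysts could each follow the text, obtain different event counts and report different primary results. The surgical team is not blinded, so the choice should not be left open until the data are seen.

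The planning rates raise a second question. They are given for groin SSI of any depth. If the tested endpoint were narrower, the control rate, and probably the difference between arms, would be smaller than planned.

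**Working it through.** **1. The passages side by side**

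| Place | Depth of SSI | Window |
|---|---|---|
| Primary endpoint sentence | superficial | 30 days |
| CDC wording in the same section | involves skin and subcutaneous tissue; does not say only these | 30 days |
| Szilagyi grading in the same section | I dermal, II subcutaneous, III arterial graft | none given |
| Secondary endpoints | deep | 90 days |
| Abstract; hypothesis | not limited | 30 days |
| Blinded assessment; Sample size; Statistical analysis | not limited | none given |

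Grades I and II fall within skin and subcutaneous tissue. Grade III, and any deep infection that spares the superficial layers, is where the readings part.

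**2. The plan's own sample size**

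Inputs: p1 = 0.30, p2 = 0.06, alpha 0.05 and 80% power (Sample size); two-sided tests (Statistical analysis); Fleiss method with continuity correction (Sample size). Hence d = 0.24 and the mean rate p̄ = 0.18.

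- Uncorrected: n′ = [1.960·√(2·0.18·0.82) + 0.842·√(0.30·0.70 + 0.06·0.94)]² / 0.24² = (1.0649 + 0.4344)² / 0.0576 = 39.0.
- Corrected: n = (n′/4)·[1 + √(1 + 4/(n′·d))]² = 47.0, so 47 per group. Rounding n′ up to 40 first gives 47.97, the stated 48.
- Allowance: 48 / 0.90 = 53.3, so 54 per group and 108 in total, as stated.

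The sample size therefore reproduces for the any-depth rates.

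**3. Power at 48 per group under each reading**

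Power = Φ{[d − 1/n − 1.960·√(2p̄(1−p̄)/n)] / √[(p1(1−p1) + p2(1−p2))/n]}.

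For 30% v 6%: (0.2192 − 0.1537) / 0.0745 = 0.879, giving 81%.

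For a superficial-only endpoint, some share s of SSIs must be removed. The documents do not give s, so 10% to 30% is assumed, in two versions: removed from controls only (NPWT rate stays at 6%), or from both arms.

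| Assumed s | Controls only: rates | Power | n needed | Both arms: rates | Power | n needed |
|---|---|---|---|---|---|---|
| 0 | 30% v 6% | 81% | 47 | 30% v 6% | 81% | 47 |
| 10% | 27% v 6% | 71% | 57 | 27% v 5.4% | 75% | 54 |
| 20% | 24% v 6% | 59% | 72 | 24% v 4.8% | 67% | 62 |
| 30% | 21% v 6% | 46% | 94 | 21% v 4.2% | 59% | 72 |

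n needed is per group for 80% power before the 10% allowance. With all 54 per group evaluable, power is 77%, 66% and 52% (controls only) or 81%, 74% and 65% (both arms).

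**The case against.** The strongest reply is that the defining section is broader than its first sentence. It asks for infection involving skin and subcutaneous tissue, not infection confined to them. It accepts purulent drainage, a culture from the incision, opening by a surgeon or a physician's diagnosis. A deep or graft infection that also involves the incision can meet those criteria, and grading up to III suggests that the authors expected such cases among the counted events. The other sections may simply be using the term as defined there. Deep SSI to 90 days, SSI needing surgery, amputation and death are all recorded as secondary outcomes.

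Much of this stands. A reader might infer that every deep or graft infection would count as a treatment success; the text does not support that. It supports only that some could be primary non-events, and even those would still appear among the secondary outcomes. A reader might also infer that the sample size is wrong; it is right for SSI of any depth.

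Nor can the Discussion's remark on grades anchor a deep share. It gives no breakdown for the control cohort, and grade II is subcutaneous, so it lies inside the superficial definition.

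The reply does not remove the contradiction. Deep SSI is set apart as a secondary endpoint, which makes it hard to treat superficial as a stray word, and grade III still does not belong under it.

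**Conclusion.** The primary endpoint contradicts itself on depth, and the contradiction can change which events are counted. This needs correction before analysis. It rests on the text alone and on no assumption.

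The effect on power is conditional. Under the any-depth reading there is none. Under the superficial-only reading, power at 48 per group is below the stated 80% at every share examined: 46% to 71% if deep infections occur in controls only, and 59% to 75% if the share is equal in both arms. These are illustrations over an assumed share of 10% to 30%, not estimates. At the mildest setting (10% in both arms, no losses from 54 per group) power would still be about 81%.

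**What to change.** In Definition of primary endpoint and outcome measures, delete superficial and define the primary endpoint as any SSI of the groin incision (Szilagyi I to III) within 30 days. This matches the abstract, hypothesis, sample size and analysis, and leaves 48 and 54 per group unchanged. Report superficial and deep SSI as components, and keep deep SSI to 90 days as a secondary endpoint.

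Trial status reports 46 patients already enrolled, and treatment is open-label. The change should therefore be a dated clarification, with its reason, decided without reference to outcomes by arm.

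If superficial SSI alone is truly intended, use that term in every section, restate the planning rates and power for it, and say how deep and graft infections within 30 days are counted.

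The preferred change costs one sentence and a dated record. It needs no extra patients and uses assessments and grading already planned. The alternative would probably require a larger sample.
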